#### 2.2.1. Inclusion and Exclusion Criteria

The registry will enroll consecutive patients who must meet all the following inclusion criteria:Age ≥ 1 year.Confirmed diagnosis of allergic rhinitis, conjunctivitis, and/or allergic asthma according to EAACI 2019 guidelines [21]. The confirmation of allergenic sensitization must be documented by skin prick tests and/or serum specific IgE.Having been followed by the recruiting center for at least one month. This is considered necessary to establish that the patients are genuinely affected by allergic respiratory disease and are eligible for AIT; in this period, screening tests are carried out to exclude and/or confirm concomitant diseases (comorbidities). In fact, according to the aforementioned EAACI guidelines [21], a patient can be defined as genuinely eligible for AIT only after a preliminary phase in which the patient is treated with a therapy targeted to the clinical manifestations. This observation period allows a correct evaluation of the real adherence and response to therapy, as well as the identification and appropriate treatment of any comorbidity and the possible elimination of aggravating factors.Having received the prescription of any of the available AIT products in Italy, irrespectively of the selected allergens and the administration route and schedule.

There will be no exclusion criteria to allow a real-life vision of the characteristics of these patients eligible for or treated with AIT.

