#### 2.2.3. Objectives

Our objectives include the following:○Evaluate the short- and long-term real-life effectiveness and safety of AIT overall, in specific patient groups’ phenotypes and with specific AIT products.○Evaluate the pertinence and differences in suggesting AIT to a patient, comparing the physician’s evaluation in various settings with established international guidelines, describing the factors associated with treatment choices and changing over time, and promoting interoperability, data sharing, and cross-comparison among centers.○Describe long-term respiratory allergic disease evolution in patients treated with AIT, especially in the pediatric population.○Describe the natural history of the patient population with respiratory allergies and identify patient groups describing their illness burden, management patterns, and clinical progression.○Promote the creation of accurate, standardized, and efficient processes for diagnosing and treating respiratory allergic diseases, especially with AIT.○Assess biomarker data to predict diagnosis, treatment response, and long-term disease progression.

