#### 2.2.5. Duration of the Study and Statistics

The aforementioned data will be collected for 10 years for each patient. Additionally, periodic statistical analyses will be conducted by the study’s central data manager. The main target will be describing the enrollment trend in the various centers, evaluating the completeness of the information collected, and quality control. The following register comprehensiveness indicators for each center will include the following: the number of patients recruited, the percentage of patients recruited compared to the expected target, and the percentage of missing data per variable. Moreover, descriptive analyses will be conducted to display the distribution of the main characteristics of patients by each center (e.g., sex, age, comorbidities, allergen sensitization profile, the severity of the disease, outcomes, ongoing therapies, etc.).

Quantitative variables will be expressed as mean and standard deviation (or median and interquartile range if distributed asymmetrically). Qualitative variables will be expressed as absolute frequencies and percentages.

The calculation of statistical power or precision is calculated on the basis of the existing sample size. The normality of the continuous variables will be evaluated with the Kolmogorov–Smirnov test. Differences between groups among qualitative variables will be analyzed with the chi-square test or Fisher’s exact test depending on their distribution. Differences between groups among quantitative variables are analyzed via Student’s t-test or Mann–Whitney, on the basis of their distribution.

A two-tailed *p*-value with values inferior to 0.05 will be considered significant. Multivariate or univariate linear regression analyses will be performed among the variables based on a 95% confidence interval. Advanced statistical models, such as the Generalized Estimating Equation (GEE) or the Generalized Linear Model (GLM), will be used to identify responders and non-responders.

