### 3.1. The Crescent Role of Real Data in Modern Medicine

In recent meta-analyses of thousands of different studies about AIT [44] and its use for AR [43] and allergic asthma [45], an essential divergence in some outcomes has been found, basically justified by the study design and different outcomes, study population, and products.

The RIAIT registry will provide many homogenous data on a vast and heterogeneous population, collecting similar, agreed, and consistent information. The openness of the inclusion criteria and the absence of exclusion criteria would lead to the acquisition of many combinations between products, patients, and disease sub-types, allowing the study of different drugs in different setups in a real-world scenario.

Moreover, to assist in the quality appraisal of observational comparative effectiveness research, in recent years a REal Life Evidence AssessmeNt Tool (RELEVANT) has been developed by the Respiratory Effectiveness Group (REG) and EAACI joint task force [46,47]; the tool was designed to identify evidence which is robust enough to inform clinical practice and to warrant consideration by guideline bodies and has been used to systematically review observational studies on the effectiveness of AIT in treating respiratory allergic diseases [48]. The study identified central defects of comparative effectiveness research on AIT and a general lack of high-quality life-effectiveness observational research, highlighting the need for robust and reliable real-life data.

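### Student's t-test is named for group differences with no provision for unequal variances; Welch's version would be a safer default at almost no cost (minor)

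*Protocol article*

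**What the plan says.** All of the following is in the protocol article.

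- Section 2.2.5 names the tests for quantitative variables: "Differences between groups among quantitative variables are analyzed via Student’s t-test or Mann–Whitney, on the basis of their distribution".
- The same section gives the check behind that choice: "The normality of the continuous variables will be evaluated with the Kolmogorov–Smirnov test". No check, condition or rule concerning variances appears.
- The threshold is a two-tailed p-value, "with values inferior to 0.05 will be considered significant".
- No group sizes or planned total are given: "The calculation of statistical power or precision is calculated on the basis of the existing sample size".
- Section 2.2.3 sets effectiveness and safety as an objective overall, and also "in specific patient groups’ phenotypes and with specific AIT products".
- Section 2.2.1 admits consecutive patients on any available product, "irrespectively of the selected allergens and the administration route and schedule", with no exclusion criteria.
- Section 3.1 expects that this openness "would lead to the acquisition of many combinations between products, patients, and disease sub-types".

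Section 2.2.5 also plans linear regression, and GEE or GLM models to separate responders from non-responders.

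**The concern.** Student's t-test estimates one common variance from both groups. When the SDs differ and the groups differ in size, the pooled estimate is dominated by the larger group and the standard error of the difference is wrong. If the smaller group is the more variable one, the standard error is too small and differences are declared too often. If the larger group is the more variable one, it is too big and real differences are missed.

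A normality check cannot detect this, because two perfectly normal groups with different SDs pass it and go to the pooled test. More patients do not cure it either: the bias depends on the ratios of sizes and SDs, not on the total. In a registry that takes patients as they come, common and rare products will form groups of different size, and a mixed population makes unequal spread plausible. A default test should not rest on equal variances here.

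**Working it through.** **Inputs from the article.** Two-sided 5% level; Student's t-test for normally distributed variables (section 2.2.5). The article states no group size, size ratio, SD or power, so beyond the nominal 5% there is no figure to reproduce.

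**Assumptions.** Normal data, no true difference, size ratio k = n(larger)/n(smaller) from 1 to 10, and SD ratio r = SD(smaller group)/SD(larger group) of 1.5 or 2 in either direction.

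**Formula.** In large samples the true variance of the mean difference, divided by the variance that the pooled test assumes, is

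R = (k·r² + 1) / (r² + k), and the true error is 2·[1 − Φ(1.96/√R)].

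**When the test is sound.** With equal SDs (r = 1), R = (k + 1)/(1 + k) = 1. With equal sizes (k = 1), R = (r² + 1)/(r² + 1) = 1. Either condition alone keeps the error at 5%.

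**Worked cases.**
- 2:1, smaller group with twice the SD: R = (8 + 1)/(4 + 2) = 1.5; 1.96/√1.5 = 1.600; error 11.0%.
- 2:1, larger group with twice the SD: R = (0.5 + 1)/(0.25 + 2) = 0.667; 1.96/√0.667 = 2.400; error 1.6%.
- 10:1, smaller group with twice the SD: R = 41/14 = 2.929; 1.96/√2.929 = 1.145; error 25.2%.
- 10:1, larger group with twice the SD: R = 3.5/10.25 = 0.341; 1.96/√0.341 = 3.354; error 0.1%.

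**True error of the nominal 5% Student test, by formula.**

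| Size ratio | Smaller group more variable, SD ratio 1.5 / 2 | Larger group more variable, SD ratio 1.5 / 2 |
|---|---|---|
| 1:1 | 5% / 5% | 5% / 5% |
| 2:1 | 8.5% / 11.0% | 2.6% / 1.6% |
| 3:1 | 10.7% / 15.0% | 1.7% / 0.8% |
| 4:1 | 12.1% / 17.9% | 1.3% / 0.4% |
| 9:1 | 15.4% / 24.5% | 0.7% / 0.1% |
| 10:1 | 15.7% / 25.2% | 0.7% / 0.1% |

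**Check by simulation.** For ratios up to 9:1, with 100,000 replicates per case and a smaller group of 20, 50 or 200, the simulated error of Student's test agreed with the formula to within about 0.3 percentage points. At 30 against 300, 20,000 replicates gave 15.7% and 25.1% (smaller group more variable), and 0.6% and 0.1% (larger group more variable).

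**Welch's test on the same data.** It stayed between 4.9% and 5.2% in every case from 1:1 to 9:1. At 30 against 300 it also gave 4.9% to 5.2%.

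**Cost of Welch when SDs are in fact equal.** It has fewer degrees of freedom. For 30 against 300, taking both sample variances as equal, these are (1/30 + 1/300)² / [(1/30)²/29 + (1/300)²/299] = 0.0013444/0.00003835 ≈ 35, against 328 for Student. The critical values are 2.03 and 1.97, a difference of about 3% even at this imbalance.

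**The case against.** Five arguments weigh against the point.

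1. **Unequal size alone does no harm.** This stands. A reader might infer that uneven product groups by themselves push the error to 16–25% or below 1%. They do not: with equal SDs the error is 5% at every size ratio. Unequal SDs are the second necessary condition. The article reports no SDs, and a different patient mix may shift means without changing spread by a factor of 1.5 or 2.
2. **The largest figures come from the extreme end of the assumptions.** This stands. Errors of 15% or more need about 9:1 with an SD ratio of 1.5, or 3:1 with a ratio of 2.
3. **The t-test is not the only method, and no objective is assigned to it.** This also stands. Mann–Whitney is the stated alternative, and many questionnaire scores and biomarkers may go there. Section 2.2.5 also says "Multivariate or univariate linear regression analyses will be performed among the variables based on a 95% confidence interval", adds GEE and GLM, and describes its periodic analyses as mainly concerned with recruitment, completeness and quality. A reader might infer that the product and phenotype comparisons will be decided by an unadjusted t-test; the article does not say so. Mann–Whitney is not a full escape, however. With a smaller group of 50 it rejected in 9% to 13% of simulations at 4:1 to 9:1 when the smaller group was the more variable one (SD ratio 1.5 to 2), and in 0.8% to 1.8% in the reverse direction at SD ratio 2. Whether those rejections count as errors is debatable, since the classical Mann–Whitney null hypothesis is that the distributions are identical.
4. **This is a condensed article, and the t-test variant could be left to an analysis plan.** This holds only in part. The article does not stay silent: it names a test, and that name ordinarily means the pooled version. An analysis plan that follows the wording would inherit the weakness.
5. **Changing the rank test or the regression standard errors goes further than the evidence.** This stands. No defect in the planned regressions has been shown, and the choice of rank test is largely preference.

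**Conclusion.** The point holds in limited form. The article names a pooled-variance test, selects it by a normality check alone and makes no provision for unequal variances, in a registry where group sizes are left to chance. If sizes differ by 2:1 to 10:1 and SDs by a factor of 1.5 to 2, the nominal 5% error becomes something between about 0.1% and 25%. At 2:1 it is about 1.6% to 11%. These ratios are assumptions; only the uncontrolled group sizes follow from the article. The documents do not show that SDs will differ, nor that any objective will be settled by this test. Severity is minor: a better default is available nearly free, and no demonstrated error in the planned results is claimed.

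**What to change.** In section 2.2.5, name Welch's (unequal-variance) t-test as the default in place of Student's t-test, without a preliminary test of variances.

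The change is one of wording. It needs no extra data, and standard software provides the test. When variances are equal the loss of power is very small; it grows only when one group is both very small and far outnumbered. A rank test that allows for unequal spread (Brunner–Munzel) and heteroscedasticity-robust standard errors in the linear regressions are optional additions and are not needed to resolve this point.

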#### 2.2.6. Electronic Database, Data Management, and Confidentiality

The study data will be collected and managed via a specific eCRF accessible from the web. The eCRF is implemented by the REDCap^®^ software installed by the Italian Society of Asthma Allergology and Clinical Immunology (SIAAIC) and the Italian Society of Pediatric Allergy and Immunology (SIAIP). REDCap^®^ is a secure, web-based software platform created to support data collection for research purposes, providing the following: an intuitive user interface for validated data collection; audit trails to record any data manipulation and data export procedures; automatic export procedures in pseudo-anonymous format compatible with the most common statistical software; and data integration procedures and interoperability with external resources [37,38].

Each user of a center involved in the project receives an email with their username and must define their password. Through this “table-based” authentication method, the user passwords are stored in the database in an encrypted format using the SHA-512 hash function. Authentication is also secure thanks to an HTTP connection based on an SSL certificate. Through their credentials, each user can access a reserved area of the web application. The actions enabled for each user will depend on the administrator’s role associated with the user (data entry, data monitoring, etc.). The application generates a unique and pseudo-anonymous identification code for each patient. Each center maintains the enrollment list locally, based on the association between the identification data of the enrolled patient and the unique pseudo-anonymous code. No patient identification information will be stored within the database in accordance with the principle of data minimization and compliance with the general data protection regulation (GDPR, General Data Protection Regulation—EU Regulation 2016/679). The data ownership lies with the participating centers, SIAAIC and SIAIP.

#### 2.2.7. Ethics

The latest revision of the Helsinki Declaration, as well as the Oviedo Declaration, are the basis for the ethical conduct of the study. The study protocol is designed and will be conducted to ensure adherence to the principles and procedures of Good Clinical Practice and to comply with Italian laws, as described in the following documents and accepted, with their signature, by the study investigators:ICH Harmonized Tripartite Guidelines for Good Clinical Practice 1996.Directive 91/507/EEC, The Rules Governing Medicinal Products in the European Community.Legislative Decree n.211 of 24 June 2003.Legislative Decree n.200 of 6 November 2007.Ministerial Decree 21 December 2007.

The study protocol has been approved by the Central Ethics Committee (Comitato Etico Indipendente Humanitas, protocol number: 2732/2020, and subsequent amendments) and the enrollment in the other centers will start upon approval of each local Ethics Committee.

Together with the British Society for Allergy & Clinical Immunology (BSACI) Registry for Immunotherapy (BRIT) [39] and the international South-Eastern European Adverse Events Registry (ADER) [40,41], this is one of the first registries of patients who are eligible for and benefit from AIT that has been established and this will be a pilot project to be shared with other countries through the European Academy of Asthma Allergy and Clinical Immunology (EAACI) [42].

Inclusion criteria, observation time, and data collected are summarized in Figure 1.

## 3. Discussion

Allergen immunotherapy has been one of the cornerstones of the treatment of the most significant allergic respiratory diseases for years and it is cited in papers written by the major national and international societies that deal with recommendations and guidelines on the treatment of these pathologies, as can be seen in the EAACI guidelines on AIT in allergic rhinoconjunctivitis [20], Italian guidelines [30], and Global Initiative for Asthma (GINA) recommendations [22].

Nevertheless, in the same papers, various issues have been addressed, questioning the quality of the studies that eventually led to the approval of this therapy by organizations and emphasizing the differences in the various pharmaceutical products prescribed. Therefore, many open questions have been pointed out, and those unanswered queries remain controversial [43]. We think that the RIAIT registry might provide a substantial number of data, and therefore statistical power, sufficient to address these criticisms, as well as answer important research questions, standardize data, provide tools to deal with the unmet needs, and offer solid scientific foundations for future standards about AIT.

### 3.1. The Crescent Role of Real Data in Modern Medicine

In recent meta-analyses of thousands of different studies about AIT [44] and its use for AR [43] and allergic asthma [45], an essential divergence in some outcomes has been found, basically justified by the study design and different outcomes, study population, and products.

The RIAIT registry will provide many homogenous data on a vast and heterogeneous population, collecting similar, agreed, and consistent information. The openness of the inclusion criteria and the absence of exclusion criteria would lead to the acquisition of many combinations between products, patients, and disease sub-types, allowing the study of different drugs in different setups in a real-world scenario.

Moreover, to assist in the quality appraisal of observational comparative effectiveness research, in recent years a REal Life Evidence AssessmeNt Tool (RELEVANT) has been developed by the Respiratory Effectiveness Group (REG) and EAACI joint task force [46,47]; the tool was designed to identify evidence which is robust enough to inform clinical practice and to warrant consideration by guideline bodies and has been used to systematically review observational studies on the effectiveness of AIT in treating respiratory allergic diseases [48]. The study identified central defects of comparative effectiveness research on AIT and a general lack of high-quality life-effectiveness observational research, highlighting the need for robust and reliable real-life data.

The discussion on the possible use and the value of these data fits within the broader topic of the validation of real-life studies in the context of modern medicine. In a recent manifesto endorsed by other scientific organizations such as the World Allergy Organization and International Primary Care Respiratory Group [25], real-world (RW) studies, such as registries, are described as essential tools to assess the drugs’ “effectiveness” (defined as the actual effects in the RW/clinical practice) as opposed to randomized controlled clinical trials (RCTs) responsible for defining the drug’s “efficacy” (the effect in artificial conditions as randomized controlled clinical trials). For instance, in asthma, real-life studies have been showing results sometimes significantly divergent from the ones collected from RCT, due to differences between trial and real-life patients in many aspects crucial to predicting the treatment response (such as therapy adherence, body mass index, comorbidity, and race) [49,50,51,52]. Therefore, as promoted by the Respiratory Effectiveness Group, the RCTs and real-life research should be considered complementary [24,53]; registries possess the potential to determine whether results observed in RCTs can be applied to a broader and heterogenous population, or whether other hypotheses should be considered and tested (e.g., for instance, treatment effectiveness in subgroups of interest, safety in a wide range of populations, and cost-effectiveness in various healthcare systems).

The aforementioned statements refer to the broader debate on the “efficacy-effectiveness gap”, identified as the discrepancies between the outcomes reported in RCTs and those observed in real-world clinical practice [54,55,56,57]. Of course, RCTs remain the cornerstone of modern evidence-based medicine and are still considered the gold standard for high-quality research. Nonetheless, RTCs suffer from intrinsic limitations: firstly, strict inclusion criteria, which make the findings obtained challenging to apply to real-life and larger populations; secondly, a relatively short duration in time, generally insufficient when there is the will to understand the long-time effects of a therapy on a patient.

Registries present some limitations as well, especially if compared with RCTs; they do not provide randomization of patients, there might be missing or incomplete data, the enrolment of patients in registries is less supervised compared with RCT, and the follow-up presents a lower grade of standardization [58].

Considering the limitations and unique opportunities that this kind of study might provide, numerous registries have been created for severe asthma, designed to understand better the epidemiology, inflammatory profile, different phenotypes, and treatment characteristics. In Europe only, the Belgian Severe Asthma Registry (BSAR) [59], the German National Registry for Asthma (GAN) [60], and the Severe Asthma Network in Italy (SANI) [61] have been formed. Considering only the latter example, many insightful data have been collected during the years, becoming the foundation for a crescent number of articles on both clinical (such as the higher-than-predicted prevalence of bronchiectasis among severe asthmatics [62]) and pharmaco-economics aspects (such as the excessive use of oral corticosteroids [63] and its impact [64]), to name a few. These register-obtained data and the following scientific publications contributed to paying attention to the revealed criticalities, setting the trends for future corrections on the current guidelines, and suggesting original goals to deal with the novel real-world needs [65]. We expect that a similar initiative like the RIAIT registry might achieve the same success in delivering reliable and easily usable data in a real-world scenario [23].

To our knowledge, together with the BSACI Registry for Immunotherapy (BRIT) [39] and the international South-Eastern European Adverse Events Registry (ADER) [40,41], RIAIT is one of the first registries of patients using AIT. Keeping asthma as an inspiring example of the utility of registries, RIAIT could serve as a pilot project for further wider collaboration in analogy with the successful International Severe Asthma Registry (ISAR) [66].

